# Effects of a smartphone app-augmented treatment for children with oppositional defiant disorder / conduct disorder and peer-related aggressive behavior – a pilot study

**DOI:** 10.1186/s13063-022-06325-6

**Published:** 2022-07-08

**Keywords:** Smartphone app, Children, Aggressive behavior, Cognitive behavioral therapy, Therapy homework, Adherence

## Abstract

**Background:**

Social competence training interventions, especially child-focused ones, have proven to be effective in the treatment of children with conduct disorder. Therapy homework assignments implemented between the therapy sessions are essential for practicing strategies developed during treatment sessions and transferring them to everyday life. However, clinical experience shows that patients’ adherence regarding these assignments is often low, thus diminishing the treatment success. One obstacle in this regard is a lack of motivation. The use of smartphone apps in the context of child and adolescent psychotherapy is relatively new, and may provide novel ways to improve the transfer of coping strategies to daily life between treatment sessions. However, only a small number of high-quality studies have analyzed the systematic use of smartphone apps in therapy. The present study will therefore evaluate patients’ homework assignment adherence when using a smartphone app as compared to a paper-and-pencil method.

**Method:**

The study will be conducted as a randomized controlled trial to evaluate the impact of a smartphone app on the adherence to therapy homework assignments (*n* = 35) in the treatment of children with aggressive behavior aged 6–12 years compared to paper-and-pencil homework assignments (*n* = 35).

**Discussion:**

This trial is intended as a pilot study and aims to provide a basis for a subsequent multicenter trial. However, the results may already lead to recommendations for the development and use of mental health-related smartphone apps for children and adolescents with aggressive behavior problems.

**Trial registration:**

Trial registration AUTHARK: German Clinical Trials Register (DRKS) DRKS00015625. Registered on 15th October 2019.

**Supplementary Information:**

The online version contains supplementary material available at 10.1186/s13063-022-06325-6.

## Background

Various interventions have been proven to be effective for the treatment of children and adolescents with oppositional defiant disorder (ODD) and conduct disorder (CD). In particular, studies have demonstrated the effectiveness of child-focused interventions (social competence training), parent-focused interventions (parent management training), combined child-parent interventions, and multimodal or multi-component programs [1, 2].

Child-oriented approaches within cognitive behavioral therapy (CBT) usually include at least one of the following: techniques to reduce or regulate excessive anger; learning social problem-solving strategies; and developing or practicing social skills as an alternative to aggressive behavior [3]. In Germany, two programs have been developed and evaluated for the treatment of children with ODD/CD and peer-related aggression. The Treatment Program for Children with Aggressive Behavior (THAV) [4] is an individualized social competence training program for children aged 6–12 years, with a distinct focus on peer-related aggression. The THAV program has been found to show significant moderate effects on peer-related aggression as rated by parents compared both to a waiting period [5] and to an active control group [6]. The Social Computer-assisted Training for Children with Aggressive Behavior Problems (ScouT) is an individually delivered, computer-assisted social skills training intervention for children with aggressive behavior [7]. The ScouT has likewise been shown to be effective with regard to parent-rated, peer-related aggression compared to a waiting period [8] and to an active control group [9].

However, despite the moderate effects of these interventions, their effects are limited. A major cause of this limited effectiveness may lie in the low adherence to therapy homework assignments aimed at improving the transfer of treatment effects from the therapeutic session to patients’ daily lives. A meta-analysis revealed that the extent to which a patient completed therapy-related assignments between therapy sessions correlated with the treatment outcome [10]. Therapy homework enables patients to apply newly gained social competences in real life. Moreover, the patient’s experiences with these homework assignments are reflected upon during subsequent therapy sessions, thus providing the therapist with important diagnostic information [11, 12].

A study evaluating the treatment processes during the THAV program reported a significant correlation between the total score of a child's adherence (cooperation and implementation of homework) and the reduction in parent-rated oppositional behavior [13]. However, in the evaluation of the ScouT program, no significant correlations were found between child or parental adherence and the reduction in aggressive symptoms [14].

The problem of therapy homework adherence (THA) is not restricted to the treatment of children with externalizing behavior problems, but is also found in the treatment of children and adolescents with other mental disorders [15, 16]. New technologies, such as smartphone apps, may provide novel opportunities to improve THA and may also enhance research options in this field [17].

Smartphone apps can support patients with their therapy homework in everyday life (e.g. arranging to meet up with a classmate) by reminding them of the tasks via push messages or by providing instructions for their implementation. Moreover, they help patients to record real-life experiences using electronic diaries. Reward systems within a smartphone app enable direct feedback on completed tasks, and may consequently also enhance THA [18]. With regard to research options, smartphone apps can provide momentary assessment functions in order to examine current emotional states, cognitions or behavior, and may thus reduce the recall bias [19, 20].

In 2017, Grist et al. [21] identified 15 mental health-related smartphone apps for preadolescents and adolescents which had been described in publications. Most of these apps contained self-observation functions (mood, emotions, behavior), but only one app provided instructions for an active intervention in the form of exposure (The Mayo Clinic Anxiety) [22]. Five of the 15 apps were described as a supplement to face-to-face treatment: Mobile Mood Diary [15], SmartCAT [23], Safety Plan [24, 25], The ACT App [26], an unnamend app [27].

Another systematic review of smartphone-based symptom monitoring and interventions for children, adolescents, and young adults with various mental health disorders identified 15 studies that evaluated a total of 14 different apps [28]. Only eight of these apps included specific treatment content in addition to mood and behavioral monitoring [25, 29–35]. Moreover, only three of the identified studies used a randomized control group design with more than 20 patients within each treatment arm in order to evaluate the effectiveness of an app-augmented treatment compared to a treatment-as-usual intervention group [25, 29, 32].

Furthermore, little research has explored the use and implementation of app content between therapy sessions in greater depth [15, 36]. Although eight of the 15 studies in the systematic review by Melbye et al. [28] reported results on adherence and app acceptance during treatment periods, the studies differed somewhat in how adherence was described (e.g., percentage of tasks completed versus required, achievement of a given skill level). Moreover, adherence usually refers only to the number of tasks completed and not to how users actually perform these tasks [28].

Further studies also generally related app adherence to the number of tasks completed. For example, Kaur et al. [37] found that depressive adolescents used a self-monitoring function of a smartphone app frequently, and in a small pilot study, Mathews & Doherty [15] found an average THA of 65% for completing a daily mood diary.

The SmartCAT app [23] was designed to enable and motivate patients to practice skills outside of therapy sessions. In a small feasibility trial, children and adolescents with anxiety were instructed to use the skills coach when they felt anxious or when they received a reminder from their therapist in the form of a text message. Participants completed an average of 5.36 entries out of 6.48 requests (82.8% completion rate) between each session (SD = 1.95). On average, they spent 3.44 min (SD = 0.98 min) completing the skills coach entries.

To the best of our knowledge, only one study has specifically focused on THA within app-augmented CBT for youth with depression [16]. In an ongoing multisite, randomized controlled pragmatic clinical trial, the authors are evaluating the influence of the app on homework completion. The authors assume that participants who receive the app-augmented treatment will show greater homework compliance. Due to the low compliance rates so far, the app is expected to have moderate effects. For the group comparison across four measurement points, a power of 0.84 was calculated for a sample size of 35 per group (app, no app) to determine effects of homework compliance at α = 0.5. No other results from this study were available for review at the time of submission of this study protocol.

Despite the large number of mental health-related smartphone apps for children and adolescents, only a few have been evaluated in terms of their effectiveness using clinical samples [38]. To date, moreover, there is no methodologically sophisticated study on the use of smartphone apps in the therapy of children with aggressive behavior problems [39, 40], and hardly any consideration has been given to the effects of smartphone apps on therapy homework adherence [18, 41].

Therefore, this pilot study aims to bridge this research gap by evaluating a smartphone-augmented CBT intervention for children with aggressive and oppositional behavior problems with a newly developed app (App-unterstützte Therapiearbeit für Kinder, AUTHARK).

The primary objective of the AUTHARK study is to determine whether participants who receive a smartphone-augmented therapeutic intervention show significantly higher adherence regarding the quantity and quality of completed therapy homework assignments than participants who receive a similar treatment without the support of a smartphone app.

In detail, this study will examine the following hypotheses:1) The experimental group (THAV/ScouT + AUTHARK) will show stronger adherence (implementation of therapy homework assignments (THA)) than the control group (THAV/ScouT), as assessed after each therapy session using the Questionnaire for Therapy Adherence [42] (primary outcome).2) The experimental group (THAV/ScouT + AUTHARK) will show a stronger reduction in aggressive symptoms than the control group (THAV/ScouT) (assessed using the parent-, teacher-, and patient-rated DISYPS-III Symptom Checklist for Disruptive Behavior Disorder (SCL-DBD parent, SCL-DBD teacher, SCL-DBD patient (ages 11–18) [43] and using the individual problem list from the THAV program [4]).3) The experimental group (THAV/ScouT + AUTHARK) will show a stronger reduction in comorbid symptoms than the control group (THAV/ScouT) (assessed using the total score of the German version of the Child Behavior Checklist for ages 6–18 (CBCL/6-18R-total) [44], the total score of the German version of the Teacher’s Report Form for Ages 6–18 (TRF/6-18R-total) [45], the total score of the German version of the Youth Self Report for ages 11–18 (YSR/11-18R-total) [46], and the parent-, teacher-, and patient-rated DISYPS-III Symptom Checklist for Attention-Deficit/Hyperactivity Disorder (SCL-ADHD parent, SCL-ADHD teacher, SCL-ADHD patient (ages 11–18) [43]).4) Patients in the experimental group (THAV/ScouT + AUTHARK) will show a stronger improvement in psychological functions that help to reduce aggressive symptoms (social-cognitive information processing, impulse control, social skills, empathy) than patients in the control group (THAV/ScouT) (assessed using the parent- and patient-rated Questionnaire on Aggressive Behavior in Children (FAVK parent, FAVK patient (ages 9–12) [47], the parent- and patient-rated Inventory of Callous-Unemotional Traits (ICU parent, ICU patient (ages 8–12) [48] [49], and a Social Problem-Solving Test for children ages 6–12 (SPST) [7].5) Patients in the experimental group (THAV/ScouT + AUTHARK) will show a stronger improvement regarding psychosocial functioning and quality of life than patients in the control group (ScouT/THAV) (assessed using the parent-rated modified German version of the Weiss Functional Impairment Rating Scale Parent Report (WFIRS-P-M) [6], the revised parent- and patient-rated Questionnaire for Measuring Health-Related Quality of Life in Children and Adolescents KINDL-R parent, KINDL-R patient (ages 7–13) [50], and the parent- and patient-rated Questionnaire for the Assessment of Adaptive and Maladaptive Emotion Regulation Strategies (FRUST parent, FRUST patient (ages 8–12)) [51].6) Patients and parents/caregivers in the experimental group (ScouT/THAV + AUTHARK) will show higher treatment satisfaction than those in the control group (ScouT/THAV) (assessed using the modified German version of the Client Satisfaction Questionnaire (ZUF-8-M) for parents/caregivers and patients [52]).

A detailed description of the above-mentioned clinical assessment tools is provided in the section “Secondary Outcomes”.

In addition, we will address the following research questions:How feasible is the AUTHARK smartphone app and how satisfied are patients and parents/caregivers with the app?What is the clinical significance of the symptom change in the experimental group compared to the control group?Which moderators/predictors (e.g., gender, age, parental mental health, adverse childhood experiences) can be identified to predict treatment outcome?

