### Recruitment, inclusion and exclusion criteria

Patients for the AUTHARK study will be recruited from three different sites: (1) the outpatient units of the Department of Child and Adolescent Psychiatry and of the School of Child and Adolescent Behaviour Therapy (AKiP) at the University Hospital Cologne, (2) primary and special education schools and (3) pediatric and psychiatric practices in Cologne, Germany.

Participants will be included if they meet the following inclusion criteria: (1) child age: 6;0 to 12;11 years at T1; (2) clinician-rated diagnosis of ODD/CD based on a structured interview (ILF-EXTERNAL) that is part of the comprehensive Structured Interview for Children and Adolescents according to ICD-10 and DSM-5 from the DISYPS Systems (DISYPS- ILF) [53] at T1; (3) parent-rated ODD/CD symptoms from the parent-rated DISYPS III Symptom Checklist for Disruptive Behaviour Disorder (SCL-DBD parent) [43] with a stanine score of 7 or higher at T1; (4) peer-related aggressive (verbal and/or physical) behavior must be reported by the parents/caregivers at T1; (5) willingness and ability (e.g. sufficient knowledge of German, sufficient competence in using a smartphone) of patient and parents/caregivers to participate in the intervention; (6) children treated with a stable dose of psychotropic medication (e.g. methylphenidate) will be included in the trial. Criteria (2) and (3) will also be evaluated again at T3. If these two criteria no longer apply to the patients at T3, the study participation will be terminated.

The following exclusion criteria will be applied and evaluated at T1: (1) child’s intelligence is below average (IQ < 85) based on a standard intelligence test (German version of the Culture Fair Intelligence Test, Primary Intelligence Scale 1 (CFT 1-R) [54] and Scale 2 (CFT 20-R) [55]; (2) Autism spectrum disorder or other severe comorbid disorder which dominates the clinical picture according to clinical rating; (3) Current or planned inpatient psychotherapy or outpatient behavioral parent management training on a weekly/biweekly basis; (4) Low level of German language skills of the patient or the parents/caregivers.

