#### Participant timeline

The individual study duration per patient is between five and seven months. Measurements will take place according to a specific schedule. The trial consists of three general parts: a screening process, the intervention period, and the follow-up assessment. Through an initial investigation using standardized telephone screening, a broad assessment of the inclusion and exclusion criteria will be conducted. Shortly after this initial investigation, the pre-treatment measurement (T1) will occur, which involves a detailed examination of the inclusion and exclusion criteria. After being randomized to the experimental or control group, all patients will undergo a first treatment phase (1), consisting of eight patient sessions and two to three parent/caregiver sessions, followed by an intermediate assessment (T2). Subsequently, another treatment phase (2) will be carried out, followed by a main assessment (T3). Non-responders to the treatment (significant symptoms of OD/CDD at T3 based on the clinician-rated parent interview (ILF-EXTERNAL) [53] and on the parent rating (SCL-DBD) from the DISYPS-III [43]) will participate in a third treatment phase (3), followed by a final assessment (T4). Responders to the treatment (no significant symptoms of ODD/CD at T3) will terminate the study and take part in a first follow-up assessment (T3) eight weeks after their last session. After one year, every family will be asked to complete a follow-up survey (T5).

Therefore, four study visits (T1-T4) will take place for all children and parents/caregivers in order to complete assessments. Additionally, there will be 16 study visits for all children and four to six study visits for all parents/caregivers (treatment phases 1 and 2). Within the group of non-responders after T3, there will be a further eight visits for children and two to three visits for parents/caregivers (treatment phase 3).

At the main assessment points (T1, T3/T4), the primary outcome (THA) and the secondary outcomes will be assessed. At the intermediate assessment (T2), the primary outcome and symptoms of ODD/CD as well as comorbid conditions will be assessed using only parent- and child-report questionnaires and without a clinical interview. The primary outcome will additionally be assessed every two weeks, as the therapist will rate the children’s THA using the Adherence Questionnaire (Fig. 5).

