##### Secondary outcomes

As a secondary Outcome, we will analyze the quantity (relative ratio) and the overall quality rating separately. Additionally, the percentage of tokens received from the therapists for homework compliance will be considered as a secondary outcome measure.

Further secondary outcomes listed below will be assessed at T1 (baseline) and at T3 or T4:Parent-, teacher-, and patient-rated symptoms of ODD/CD, which will be assessed using the respective rating scales: the parent-, teacher-, and patient-rated DISYPS-III Symptom Checklist for Disruptive Behavior Disorder (SCL-DBD parent, SCL-DBD teacher, SCL-DBD patient (ages 11–18)) [43]. Reliability and validity as well as the sensitivity to change of these scales have already been proven in German samples [43].Clinician-rated symptoms of ODD/CD using the Structured Interview for Disruptive Behavior Disorder (ILF-EXTERNAL), which is part of the comprehensive Structured Interview for Children and Adolescents according to ICD-10 and DSM-5 from the DISYPS-Systems (DISYPS-ILF) [53].Overall behavioral and emotional problems assessed using the total score of the German version of the Child Behavior Checklist for ages 6–18 (CBCL/6-18R-total) [44], the total score of the German version of the Teacher’s Report Form for ages 6–18 (TRF/6-18R-total) [45], and the total score of the German version of the Youth Self Report for ages 11–18 (YSR/11-18R-total) [46]. Reliability and validity as well the sensitivity to change of the German versions of these scales have been demonstrated in several studies [44].Triggering and maintaining components of aggressive behavior (social-cognitive information processing, impulse control, social skills, and reactions to the social environment) assessed using the parent- and patient-rated Questionnaire on Aggressive Behavior in Children (FAVK parent, FAVK patient (ages 9–12) [47].Parent-rated satisfaction with the treatment, assessed using the modified German version of the Client Satisfaction Questionnaire (ZUF-8-M parent), and patient-rated satisfaction with the treatment, assessed using the modified German version of the Client Satisfaction Questionnaire (ZUF-8-M patient) [61], which has been shown to be reliable, valid, and sensitive to change [62].

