
##### Predictors/moderators of treatment outcome regarding ODD/CD symptoms and impairment

As moderators or predictors of treatment outcome at T4 regarding ODD/CD symptoms and impairment, the following variables will be analyzed: (1) sociodemographic variables (e.g. place of residence, socioeconomic status; education, income, occupation and age of parents/caregivers; number of children in the family), which will be assessed through parent/caregiver interview at T1, (2) severity of comorbid disorders at T1-T3 using the patient- and parent-rated SCL-ADHD, the parent-rated CBCL/6-18R, and the teacher-rated TRF/6-18R (see above), (3) specific psychological traits of the parents/caregivers (parental aggression, depression and stress) at T1 and T3 using the FB-Ä and DASS (see above), (4) specific psychological traits of the patient (intelligence), assessed at T1 using the German version of the Culture Fair Intelligence Test, Primary Intelligence Scale 1 (CFT 1-R) [54] and Scale 2 (CFT 20-R) [55].

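### Hypothesis 3 measures comorbid symptoms partly with CBCL, TRF and YSR total scores that also contain the target aggression, so an effect on aggression alone biases those three scores towards apparent comorbidity reduction

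*Protocol article*

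**What the plan says.** The Background section of the protocol article separates two hypotheses. Hypothesis 2 is about the target problem: the app group "will show a stronger reduction in aggressive symptoms than the control group", measured with the SCL-DBD and the individual problem list. Hypothesis 3 is about comorbidity: the app group "will show a stronger reduction in comorbid symptoms than the control group (THAV/ScouT) (assessed using the total score of the German version" of the CBCL. It goes on to name the TRF and YSR totals and then the "patient-rated DISYPS-III Symptom Checklist for Attention-Deficit/Hyperactivity Disorder (SCL-ADHD parent, SCL-ADHD teacher, SCL-ADHD patient" version. The three broad-band forms are identified explicitly as total scores.

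The Secondary outcomes section gives the same totals another label: "Overall behavioral and emotional problems assessed using the total score of the German version of the Child Behavior Checklist", followed by the TRF and YSR totals. The SCL-ADHD is placed one tier lower, under Supplementary outcomes.

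The inclusion criteria require a diagnosis of ODD/CD, a parent-rated SCL-DBD stanine of at least 7, and that "peer-related aggressive (verbal and/or physical) behavior must be reported by the parents/caregivers at T1".

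The Predictors/moderators section lists "severity of comorbid disorders at T1-T3 using the patient- and parent-rated SCL-ADHD, the parent-rated CBCL/6-18R, and the teacher-rated TRF/6-18R" among the variables that may predict ODD/CD symptoms and impairment at T4.

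**The concern.** A comorbid symptom is one that exists in addition to the index disorder, and the article uses the word that way elsewhere. Under Participant timeline, "symptoms of ODD/CD as well as comorbid conditions will be assessed" at T2, as two separate things. The Discussion likewise lists ODD/CD, ADHD and further comorbid problems as distinct items.

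A score of overall behavioral problems, in children all enrolled for aggressive behavior, is the target problem plus comorbidity. Hypotheses 2 and 3 are therefore not separate on these three scores: a benefit confined to aggression would also move them. What is at stake is how the secondary results are interpreted. The study is meant to prepare a multicenter trial, and a comorbidity signal that is only the aggression signal seen again could mislead the choice of outcomes for that trial.

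**Working it through.** **Step 1: the text.** Four places bear on the same scores.

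- Background, hypothesis 3: the CBCL, TRF and YSR totals stand for comorbid symptoms.
- Secondary outcomes: the same totals stand for overall problems, with no exclusion of aggressive or oppositional content.
- Inclusion criteria: the target behavior is present in every child at T1.
- Participant timeline and Discussion: comorbidity is something other than ODD/CD.

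The first two cannot both describe the score. The third means that the difference between them matters in this sample. The article does not list the forms' items, so the inference that the totals contain the target behavior rests on the label in Secondary outcomes and on the absence of any carve-out.

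**Step 2: size, as an illustration.** The article gives no figure to reproduce here, and no SDs or correlations. Write

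Total = A + R,

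where A is the aggression part and R is everything else. Let the app shift A by d_A standard deviations and R by exactly zero. With q = SD_A / SD_R and ρ the correlation of A and R,

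d_total = d_A × q / √(q² + 1 + 2ρq).

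Inputs: d_A = 0.4, borrowed from the Sample size section, where it is not stated to be an effect on aggression. The values q = 0.25 to 2 and ρ = 0.3 to 0.7 are assumptions.

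Worked case, q = 1 and ρ = 0.5: 0.4 × 1 / √(1 + 1 + 1) = 0.4 / 1.732 = 0.231.

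| q | ρ = 0.3 | ρ = 0.5 | ρ = 0.7 |
|---|---|---|---|
| 0.25 | 0.091 | 0.087 | 0.084 |
| 0.5 | 0.161 | 0.151 | 0.143 |
| 1 | 0.248 | 0.231 | 0.217 |
| 2 | 0.321 | 0.302 | 0.286 |

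The totals would show d of about 0.1 to 0.3 while the true effect on R is zero throughout.

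**Step 3: how often this would reach significance.** For a simple two-group comparison with 35 per arm and two-sided α = 0.05 (assumed), the chance of a significant result in favor of the app is Φ(d × √(35/2) − 1.96), with √17.5 = 4.183.

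- d = 0.084: Φ(0.351 − 1.96) = about 5%
- d = 0.231: Φ(0.966 − 1.96) = about 16%
- d = 0.321: Φ(1.343 − 1.96) = about 27%

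If a score carried no target content, the corresponding figure would be 2.5%. So the estimate is shifted, but in this scenario a significant result remains the exception.

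**The case against.** The strongest reply is that the operative definition is already right. The Background refers the reader to Secondary outcomes for the description of the instruments, and that section calls the totals overall problems. On this view one loose word in a list of hypotheses is at fault. The study is also exploratory, the totals are secondary outcomes, and the primary outcome (therapy homework adherence) is untouched. All of that limits the weight of the point. It does not remove it: hypothesis 3 fixes the total scores by name as the measure of comorbidity, and an analysis that follows it faithfully will be read that way.

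Two stronger readings are tempting, and the documents support neither.

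- A reader might infer that hypothesis 3 would be declared supported whenever aggression falls. The SCL-ADHD is also a hypothesis 3 measure and the overlap argument does not apply to it. The article gives no rule by which the totals alone settle the hypothesis. The chances in Step 3 are also low.
- A reader might infer that the predictor analysis certainly repeats the overlap. The Predictors/moderators section names the CBCL and TRF without saying that the totals are used, although the article marks totals explicitly elsewhere. Which score enters, and whether T1 ODD/CD severity is a covariate, may properly be left to the analysis plan.

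It is also fair to object that the illustrated size is set by assumed inputs. That stands: only the direction follows from the text.

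**Conclusion.** The point holds for three of the four instruments named in hypothesis 3. The CBCL, TRF and YSR totals measure target plus comorbidity, so an effect on aggression alone biases them towards apparent comorbidity reduction. Under the stated assumptions the bias is about 0.1 to 0.3 SD. A different true effect on aggression scales that range in proportion. At 35 per arm it would usually not produce a significant result, so the harm is a distorted estimate and interpretation, not a likely false declaration.

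The one measure in hypothesis 3 outside the argument, the SCL-ADHD, ranks below the totals in the outcome hierarchy, so the secondary-tier evidence on comorbidity comes only from the overlapping scores. For the predictor analysis the point is conditional: it applies only if the CBCL and TRF totals are what is meant. The matter is worth correcting before analysis, but it does not threaten the primary result.

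**What to change.** 1. Base the comorbidity claim in hypothesis 3 on the SCL-ADHD and on scores from the same CBCL, TRF and YSR forms that leave out aggressive and rule-breaking content. The article does not describe the forms' subscales, so the exact scores should be named from the instrument manuals.
2. Keep the three totals as secondary outcomes under the label that Secondary outcomes already gives them, overall problems, and attach no comorbidity claim to them.
3. State in Predictors/moderators which CBCL and TRF scores are intended. If the totals are meant, use the same non-overlapping scores there and enter T1 ODD/CD severity as its own term.

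The least that would resolve the contradiction is to reword hypothesis 3 so that the totals are said to measure overall problems. The cost is scoring syntax and a few lines of text. The forms are already part of the planned assessments, so neither the sample nor the visit schedule changes.
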